### Measures

In this study, the primary outcome and secondary outcomes will be measured at baseline, the end of the 4-week treatment and the end of the 8-week follow-up. All outcome assessments will be independently performed by experienced and blinded assessors, who are also professional physical therapists.

### Primary outcome measures

#### Fugl-Meyer Upper Extremity Assessment (FMA-UE).

The Fugl-Meyer Assessment Scale (FMAS) provides a comprehensive evaluation for stroke patients with hemiplegia, covering motor, sensory, balance, joint mobility, and pain domains. In our study, we focused on the upper extremity segment, which includes 33 assessment items worth 66 points, capturing various motor aspects. This enables precise evaluation which is basic for specific therapeutic interventions for stroke patients.

### Secondary outcome measures

#### Modified Trunk Impairment Scale (mTIS).

The mTIS can be used to examine the degree of trunk control or the level of trunk impairment, which is seen as a prerequisite for balance, gait, motor function, and activities of daily living performance in stroke survivors. It comprises two distinct subscales: the Dynamic Sitting Balance Scale (DBS) and the Coordination Scale (CS). The DBS encompasses four categories, specifically assessing elbow contact with the bed on the hemiplegic and healthy sides, as well as pelvic elevation from the bed on both the hemiplegic and healthy sides. Scores for the first two categories range from 0 to 3, while scores for the latter two categories vary from 0 to 2. Meanwhile, the CS focuses on alternating forward rotations of the shoulders and knees, assigning scores from 0 to 3 for each. The total score range of this scale is 0–16, with higher scores indicative of lesser impairment in trunk control, as outlined in previous literature.

#### The Wolf Motor Function Test (WMFT).

The Wolf Motor Function Test (WMFT) will be used to evaluate the functional activity of the upper limbs. The WMFT consists of 15 items. Items 1–6 are simple joint movements while items 7–15 are compound functional movements. The WMFT score is determined based on the quality of all actions (0–5 points, six grades).

#### Functional near-infrared spectroscopy (fNIRS).

fNIRS employs a continuous-wave optical system to quantify oxygenated hemoglobin (HbO) levels in the cerebral cortex. The system utilizes a light source that emits near-infrared light at wavelengths of 690 nm and 830 nm, operating at a fixed sampling rate of 10 Hz across 95 channels. A 3D digitizer is utilized to acquire precise coordinates for each channel. These coordinates are subsequently transformed into Montreal Neurological Institute (MNI) coordinates, allowing for the projection of the data onto the standard MNI brain model using the NIRS_SPM toolbox. With this configuration, the channels are capable of covering key brain regions including the supplementary motor area (SMA), primary motor cortex (PMC), primary motor cortex (M1), primary sensory cortex (S1-S5), and dorsolateral prefrontal cortex (DLPFC) [10].

We hypothesize that seated Tai Chi Yunshou will elicit increased activation in motor-related regions (M1, SMA) and prefrontal areas (DLPFC) due to its integrated motor-cognitive demands. Raw fNIRS signals will be preprocessed using motion artifact correction (e.g., wavelet-based filtering), bandpass filtering (0.01–0.2 Hz), and conversion to hemoglobin concentrations via the Modified Beer-Lambert Law. To address multiple comparisons, we will apply false discovery rate (FDR) correction for channel-wise analyses and cluster-based permutation testing for spatial inferences. Furthermore, interhemispheric connectivity and functional remapping will be objectively quantified using coherence and correlation-based metrics between homologous channels, with graph theory approaches assessing network efficiency changes. These metrics will be correlated with clinical outcomes to link neural changes to functional recovery.

#### Barthel Index(BI).

The participants’ activities of daily living (ADL) will be evaluated during the intervention and follow-up periods using the Barthel Index (BI). Previous research has established the BI as a highly reliable tool for assessing ADLs in stroke survivors, demonstrating strong inter-rater and intra-rater reliabilities. The BI comprises 10 items that describe various daily activities, with lower scores indicating a higher level of dependency in performing these tasks.

#### Montreal Cognitive Assessment(Moca).

The Montreal Cognitive Assessment (MoCA) is a validated screening tool designed to evaluate cognitive function across six domains: memory, executive function, language, attention, calculation ability, and visuospatial skills. Administered by a trained evaluator, the test comprises a series of tasks and questions, with responses scored against standardized criteria. Total scores range from 0 to 30, where higher scores reflect superior cognitive performance. A score below 26 points is commonly used as a threshold to identify potential cognitive impairment (CI) or mild cognitive impairment (MCI), though cutoff values may vary based on educational attainment and age.

### Data management

Original study data will be prospectively collected using standardized paper-based case report forms (CRFs) at predefined assessment timepoints. Two independent data managers, both blinded to treatment allocation, will perform dual data entry into EpiData Entry Software (version 3.1) to ensure accuracy. Prior to study initiation, these personnel will complete certified training in Good Clinical Practice (GCP) standards for data management. The Data Monitoring Committee (DMC) will conduct quarterly audits verifying: (1) adherence to data handling procedures; (2) consistency between duplicate entries; and (3) protocol-defined quality control metrics. To protect participant confidentiality, all datasets will undergo full de-identification (removal of direct identifiers, replacement with non-traceable study codes) before statistical analysis. Upon completion of data collection, the finalized database will be locked via restricted access controls to prevent unauthorized modifications. Archived data will be securely stored for a minimum retention period of five years post-study completion, with limited access permitted solely for regulatory inspections or protocol-approved secondary analyses.

### Statistical analysis

Statistical analyses were conducted utilizing IBM SPSS 26.0 software. In terms of descriptive statistics, qualitative indicators were represented by percentages, while quantitative indicators were summarized using means and standard deviations. For quantitative data, an independent samples t-test was applied when the data followed a normal distribution. In cases where normality assumptions were not met, the non-parametric Wilcoxon rank sum test was employed. Qualitative data were analyzed using the chi-square test, and rank data were examined with the Wilcoxon rank sum test. For datasets containing multiple observation time points, a repeated measures ANOVA was utilized to account for the longitudinal nature of the data. Statistical significance was determined at a P-value less than 0.05. For longitudinal data violating normality/sphericity, the non-parametric Friedman test replaced repeated measures ANOVA.

Given the limited sample size (N = 84) in this study, Multiple Imputation (MI) was employed to address missing data. This method generates multiple complete datasets and pools analysis results, thereby mitigating the bias associated with single imputation in small-sample studies. All imputation procedures were conducted using the MICE package in R, with five parallel imputations performed to ensure stability.

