**Methods:**

84 stroke patients with upper limb dysfunction were randomly divided into two groups. The experimental group and the control group consist of 42 patients each. The experimental group will receive seated Tai Chi Yunshou training combined with conventional treatment, while the control group only will receive conventional training. Each training session will be implemented once a day and five times per week in a duration of 4 weeks. Primary and secondary outcomes will be measured at baseline and 4-weeks, 8-week follow-up after randomization. Fugl-Meyer Upper Extremity Assessment (FMA-UE) will be the primary outcome and Modified Trunk Impairment Scale (mTIS),the Wolf Motor Function Test (WMFT), Functional near-infrared spectroscopy (fNIRS), Barthel Index(BI) will be the secondary outcome. Functional near-infrared spectroscopy(fNIRS) will be used to explore the therapeutic mechanism.

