#### Inclusion criteria.

In accordance with the diagnostic criteria of the ‘Chinese guidelines for diagnosis and treatment of AIS’ (2018 version)and confirmed by CT or MRI examination.

First episode of stroke

Onset time between 2 weeks to 6 months

Seated balance at Level 1 or above

Unilateral limb impairment

Able to tolerate 30 minutes of seated Tai Chi Yunshou exercise and signed informed consent.

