### Sample size

This trial aims to assess the impact of Tai Chi on upper limb function in post-stroke patients. Using G-power V.3.1.9.2 software for sample size calculation, the Fugl-Meyer Assessment Upper Extremity (FMA-UE) scale was selected as the primary outcome measure. Based on data from a previously published study [18], the mean FMA-UE scores post-intervention were 60.50 ± 2.19 for the Tai Chi group and 59.14 ± 1.77 for the control group. To detect the targeted effect size of 0.6830377 with a type 1 error rate of 5% (α = 0.05) and 80% statistical power (β = 0.20), a sample size of 64 participants is deemed sufficient. Accounting for a potential dropout rate of 20%, a total of 84 participants will be enrolled, with 42 participants assigned to each group.

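### FMA-UE has no single baseline-adjusted primary contrast: the text allows an unadjusted two-group test or a repeated measures ANOVA with no deciding term or visit

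*Protocol article*

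**What the plan says.** The Abstract fixes the primary outcome: "Fugl-Meyer Upper Extremity Assessment (FMA-UE) will be the primary outcome". The Measures section gives the schedule: "the primary outcome and secondary outcomes will be measured at baseline, the end of the 4-week treatment and the end of the 8-week follow-up".

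The Statistical analysis section assigns methods by type of data, not by outcome. For quantitative data, "an independent samples t-test was applied when the data followed a normal distribution", with the Wilcoxon rank sum test where normality is not met. For repeated observations, "For datasets containing multiple observation time points, a repeated measures ANOVA was utilized to account for the longitudinal nature of the data", with the Friedman test as the fallback. The significance level is 0.05. The section names no primary test, visit, ANOVA term or covariate.

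The Sample size section works from one comparison of two means: "the mean FMA-UE scores post-intervention were 60.50 ± 2.19 for the Tai Chi group and 59.14 ± 1.77 for the control group".

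The later visit is described in two ways. The Abstract has "baseline and 4-weeks, 8-week follow-up after randomization" and the Measures section has "the end of the 4-week treatment and the end of the 8-week follow-up".

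**The concern.** FMA-UE is quantitative and observed repeatedly, so two of the section's rules cover it, and they lead to different tests. The sample size was set for a comparison of means at one post-treatment time, but the longitudinal rule points to a repeated measures ANOVA. In that ANOVA, either the group effect or the group-by-time interaction could be read as the treatment test.

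If baseline enters the ANOVA as one of three levels, randomisation makes the expected group difference there zero. The group main effect then averages in a visit with no effect. The post-only t-test has a different weakness: it discards the baseline score, which is already collected.

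Two things are at stake. One is power in a trial of 84 patients. The other is the freedom to pick, after seeing the data, among tests whose power differs widely.

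**Working it through.** **Inputs from the Sample size section.** Means 60.50 and 59.14; SDs 2.19 and 1.77; 64 evaluable patients, so n = 32 per arm; alpha 0.05.

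**Assumptions.** Tests are two-sided (sidedness is not stated). The correlation ρ is the same between any two visits (compound symmetry). The effect is zero at baseline and equal at both later visits. The documents give no correlation, so ρ = 0.3, 0.5, 0.7 and 0.8 are shown.

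**Step 1: the plan's own figures.** Pooled SD = √((2.19² + 1.77²)/2) = √3.9645 = 1.991. Then d = 1.36/1.991 = 0.683, which reproduces the stated effect size. The stated 64 does not reproduce: a two-sided t-test needs 35 per arm (70 in total) for 80.4% power. That is a separate matter. I use 32 per arm because it is the plan's figure.

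**Step 2: post-only t-test.** Noncentrality d√(n/2) = 0.683 × 4 = 2.732 on 62 df. Power is 76.7% at any ρ.

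**Step 3: ANCOVA at one visit.** The standardised effect becomes d/√(1 − ρ²) = 0.716, 0.789, 0.956, 1.138. Multiplied by 4, the noncentralities are 2.864, 3.155, 3.826, 4.554 on 61 df.

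**Step 4: ANOVA group main effect, baseline as a level.** The mean difference over three visits is (0 + d + d)/3 = 2d/3 = 0.455. The variance of a patient's three-visit mean is (1 + 2ρ)/3. The standardised effect is 0.624, 0.558, 0.509, 0.489 on 62 df.

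**Step 5: group-by-time, baseline as a level.** The squared deviations of (0, d, d) about 2d/3 sum to (2/3)d². Noncentrality is (n/2)(2/3)d²/(1 − ρ) = 7.11, 9.95, 16.59, 24.88, with 2 and 124 df.

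**Step 6: ANCOVA on the mean of both later visits.** This is the like-for-like comparator for step 5, because both use all post-baseline data. Residual variance is (1 + ρ)/2 − ρ².

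Power (%), 32 per arm:

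| Test | ρ = 0.3 | 0.5 | 0.7 | 0.8 |
|---|---|---|---|---|
| Post-only t-test | 76.7 | 76.7 | 76.7 | 76.7 |
| ANCOVA, one visit | 80.5 | 87.4 | 96.4 | 99.4 |
| ANOVA group effect | 69.0 | 59.3 | 51.8 | 48.7 |
| ANOVA group-by-time | 65.1 | 80.3 | 95.9 | 99.6 |
| ANCOVA, mean of two visits | 94.9 | 96.7 | 99.4 | >99.9 |

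**Step 7: sensitivity to n.** With all 42 per arm at full information, the t-test has 87.1%; one-visit ANCOVA 90.0, 94.6, 99.1, 99.9%; the group effect 80.6, 71.4, 63.5, 60.1%; and group-by-time 77.8, 90.4, 99.0 and over 99.9%. The pattern does not change.

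**Step 8: open visit.** If significance at either later visit at 0.05 were allowed to count, a bivariate normal calculation gives type I error of 9.1% at a between-visit correlation of 0.5 and 7.0% at 0.9. Independent tests would give 1 − 0.95² = 9.75%.

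**The case against.** The strongest reply is that this is a condensed article, that model terms and covariates normally sit in an analysis plan not shown here, and that a t-test or repeated measures ANOVA is valid after 1:1 randomisation. Validity is not in dispute. But the article does fix methods: they overlap for the primary outcome, and the longitudinal one differs from the comparison used for the sample size. That can be judged on the text as it stands.

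Other parts of the reply do limit the point. A reader might infer more than the documents support:

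- **That baseline is certainly an ANOVA level.** This follows from combining the visit schedule with the longitudinal rule. The Statistical analysis section does not say it.
- **That the plan loses power however it is read.** Group-by-time is the natural treatment test if baseline is a level. From ρ = 0.7 upward it matches one-visit ANCOVA, and at 0.8 it is marginally ahead (99.6 against 99.4%). At ρ = 0.3 the gain of one-visit ANCOVA over the t-test is only about 4 points.
- **That the plan inflates type I error to 7–9%.** It states no rule that success at either visit suffices. The figure shows what an open choice would allow.
- **That time since onset drives recovery and must be adjusted for.** The Inclusion criteria give it only as an eligibility window, "Onset time between 2 weeks to 6 months". The documents offer no evidence of its prognostic weight.
- **That the visit timings contradict each other.** The two wordings can be read as week 8 or as week 12 (4 + 8), but they can also be read alike. This is ambiguity.

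**Conclusion.** The point holds in limited form. The text leaves the primary FMA-UE test open and makes no use of baseline FMA-UE as a covariate. With the plan's effect size and 64 evaluable patients, power runs from about 49% to over 99%, depending on the test read and the correlation. The firm parts are that one-visit ANCOVA beats the post-only t-test at every correlation shown (by 4 to 23 points), and that the ANOVA group effect with baseline as a level is the weakest choice from ρ = 0.5 upward. Against group-by-time, the gain of one-visit ANCOVA is about 15 points at 0.3 and 7 at 0.5, and negligible from 0.7. All of this rests on assumed correlations, compound symmetry and an equal effect at both later visits. It should be corrected, but it does not make the planned tests invalid.

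**What to change.** State one primary analysis: the between-arm difference in FMA-UE at the end of the 4-week treatment, estimated by ANCOVA with baseline FMA-UE as covariate, or as the corresponding contrast from a mixed model with baseline as covariate. Report the adjusted difference with its 95% confidence interval. Do not let a normality check select the primary test; a rank-based comparison of the arms can be a sensitivity analysis. Make the later visit secondary, and give it one week number, counted from randomisation, in both the Abstract and the Measures section. Time since onset may be added as a prespecified covariate, but the point does not depend on it.

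No new data are needed, because baseline FMA-UE is already collected. The cost is wording plus the amendment route in the Quality control section: Steering Committee review, ethics approval and a log entry. The Trial status section says recruitment is still in progress, so the change can be made before any unblinded analysis.

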## Discussion

This study represents the first clinical trial to evaluate the effects of seated Tai Chi Yunshou exercise on patients with subacute stroke. In this trial, we assessed the impact of seated Tai Chi Yunshou training combined with conventional training compared to conventional training on upper limb function in patients with subacute stroke.

Seated Tai Chi Yunshou exhibits distinct mechanistic advantages compared to conventional rehabilitation approaches. In contrast to bilateral arm training—which often involves symmetric, rhythmic, and at times passive movement patterns—Yunshou emphasizes active and intentional control (known as “Yi” in Tai Chi philosophy), requiring continuous conscious modulation of movement quality, trajectory, and posture. Moreover, Yunshou incorporates asymmetric yet highly coordinated bimanual patterns, such as “separating hands” (Fen Shou), where one hand leads while the other follows, thereby demanding more sophisticated neural control and integration than purely symmetric movements [20]. The seated posture further facilitates integrated trunk–arm coordination through sustained subtle core activation that is dynamically coupled with upper limb movement, rather than promoting isolated limb motion. Unlike therapist-guided interventions such as proprioceptive neuromuscular facilitation (PNF), which relies on specific diagonal patterns and external resistance to evoke neuromuscular responses, Yunshou is self-initiated and depends on internal rhythm and proprioceptive feedback. This quality may enhance the engagement of internal modeling and predictive control mechanisms [21]. Additionally, the continuous and fluid nature of Yunshou, characterized by smooth transitions between movement phases, imposes unique challenges on neural timing and coordination compared to the segmented and discrete structure of PNF. We propose that the integration of continuous mindful control, asymmetric bimanual coordination, and dynamic trunk–limb synergy may uniquely foster neuroplastic adaptations and enhance interhemispheric connectivity following stroke.

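### The fallback for longitudinal data is a Friedman test, which has no group term, so when it is used the longitudinal analysis tests change over time and not Tai Chi against control

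*Protocol article*

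**What the plan says.** The Statistical analysis section of the Protocol article sets this rule for repeated measurements: "For datasets containing multiple observation time points, a repeated measures ANOVA was utilized to account for the longitudinal nature of the data". It then gives the fallback: "For longitudinal data violating normality/sphericity, the non-parametric Friedman test replaced repeated measures ANOVA". Either violation is enough to trigger it.

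The section does not say which outcomes fall under the rule. The Measures section states that "the primary outcome and secondary outcomes will be measured at baseline, the end of the 4-week treatment and the end of the 8-week follow-up", and the abstract states that "Fugl-Meyer Upper Extremity Assessment (FMA-UE) will be the primary outcome". The primary outcome therefore has three observation times.

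The question is between groups. The Discussion puts it this way: "we assessed the impact of seated Tai Chi Yunshou training combined with conventional training compared to conventional training on upper limb function".

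For quantitative data in general, Statistical analysis lists the independent t-test and adds: "In cases where normality assumptions were not met, the non-parametric Wilcoxon rank sum test was employed".

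**The concern.** A repeated measures ANOVA can carry treatment group as a between-patient factor and so test group and group-by-time. The Friedman test is a one-way, within-patient rank test. Substituting it removes the comparison that the trial was set up to make and leaves a test of whether scores move over time.

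If both arms recover to a similar degree, Friedman can be significant with no treatment effect, and that result could be reported as benefit. Running it in each arm and contrasting the two p-values is not a comparison of arms either.

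The trigger is also too wide. Failure of sphericity concerns the degrees of freedom of the within-patient F tests. It is not a reason to move to ranks or to drop the group factor.

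**Working it through.** **1. The statistic.** With n patients and k visits, rank the visits within each patient and let R_j be the rank sum for visit j:

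Q = 12 / [n k (k + 1)] × Σ R_j² − 3 n (k + 1), referred to chi-square with k − 1 degrees of freedom.

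With k = 3 and all n = 84 patients: 12 / (84 × 3 × 4) = 1/84 and 3 × 84 × 4 = 1008, so Q = Σ R_j² / 84 − 1008 on 2 degrees of freedom. With n = 42 in one arm: Q = Σ R_j² / 42 − 504. Group membership enters neither expression.

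**2. Invariance check.** On one simulated data set of 84 patients and 3 visits, the Friedman p-value was 3.07e-08. After permuting the group labels it was 3.07e-08. After adding 100 points to every visit of one arm it was again 3.07e-08. This follows from the formula and needs no assumption about the data.

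**3. The plan's own effect, for scale.** Sample size reports that "the mean FMA-UE scores post-intervention were 60.50 ± 2.19 for the Tai Chi group and 59.14 ± 1.77 for the control group". The difference is 60.50 − 59.14 = 1.36. The pooled SD is √[(2.19² + 1.77²)/2] = √3.9645 = 1.991. Then 1.36 / 1.991 = 0.683, which reproduces the stated effect size. It is a two-group difference in post-treatment means, a quantity that Friedman does not estimate.

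**4. What the fallback detects.** 2,000 simulated trials per row, 42 per arm, normal data. Assumed: SD 2.0, all within-patient correlations 0.6, change reached by week 4 and held to week 8.

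| Scenario | Friedman, pooled | Tai Chi arm significant, control not | Rank sum on change to week 4 |
|---|---|---|---|
| Equal recovery of 2 points, no effect | 100% | 0% | 4.9% |
| Equal recovery of 1 point, no effect | 99.6% | 9.2% | 5.0% |
| Arms differ by 1.36, no net time trend (+0.68 and −0.68) | 4.3% | 24.5% | 92% |

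The last row is built to isolate the group effect and is not a forecast.

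**5. Sensitivity to recovery size.** The documents give neither correlations nor a recovery size. Assumed: 42 per arm, no treatment effect, correlations 0.5 to 0.8. On the plan's SD, 0.25 SD is 0.25 × 1.99 = 0.5 points and 0.5 SD is 1.0 point.

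- 0.25 SD common recovery: Friedman significant within one arm in about 25% to 58% of trials.
- 0.5 SD common recovery: about 76% to 99% or more.
- The between-group rank sum test on change stays near 5% throughout.

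**6. How often the trigger would apply.** Mauchly's sphericity test rejects in about 5% of trials if the three correlations are equal. With unequal correlations (r between baseline and week 4, r + 0.1 between weeks 4 and 8, r − 0.05 between baseline and week 8) it rejects in about 27% to 29%, 73% and 99% at r = 0.5, 0.7 and 0.8. The range is therefore about 5% to 99%.

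Non-normality is the other route. The scale "includes 33 assessment items worth 66 points", and the planning means lie 66 − 60.50 = 5.50 and 66 − 59.14 = 6.86 points below that maximum. A ceiling effect is plausible, not certain.

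**The case against.** The strongest reply is that the plan still contains a between-group rank test. The Wilcoxon rank sum test is listed for non-normal quantitative data, the Friedman sentence does not withdraw it, and it could be applied to FMA-UE at week 4 or to change. The sample size also rests on a two-group comparison of post-treatment means. One could read the t-test and rank sum test as the comparison of arms, with ANOVA and Friedman describing the time course only. This stands to the extent that a reader might infer that the trial would be left with no test of its primary hypothesis, and the documents do not support that. It does not rescue the sentence: Friedman is the named replacement for the longitudinal analysis, and the rank sum test is tied to no visit or change score.

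The link to FMA-UE is an inference from its three visits, since Statistical analysis names no outcome. It is the plain reading, but it should be stated as a reading.

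Two further inferences also go too far. That the fallback will commonly apply cannot be shown: high rates for the sphericity test come from assumed unequal correlations. That a significant Friedman result is almost guaranteed holds for 0.5 SD recovery at the higher correlations, but not for 0.25 SD.

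The absence of a separate analysis plan does not answer the point, because the article itself names the test.

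**Conclusion.** The sentence is wrong as written and should be changed. When it applies, the longitudinal analysis loses its group comparison, and this holds whatever the data look like. The loss is confined to that analysis, because a between-group rank test remains listed elsewhere in the section.

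How often the fallback would be used, and how often it would give a significant result with no treatment effect, depends on correlations and recovery that the documents do not give. The rates above are therefore ranges under stated assumptions, not predictions.

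**What to change.** Delete the Friedman sentence and replace it with rules that keep the comparison of arms:

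- **Non-sphericity:** keep the repeated measures ANOVA with group and group-by-time terms and apply a Greenhouse-Geisser correction, or use a linear mixed model with unstructured covariance.
- **Marked non-normality:** use a between-group method. The smallest change is the rank sum test already in the plan, applied to change from baseline to week 4. Rank ANCOVA or a permutation test of the baseline-adjusted difference would also serve.

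Prescribing a single model regardless of the assumption checks would be defensible, but this defect does not require it.

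The cost is one sentence, with no extra data or patients. The Trial status section says that recruitment is still in progress, and the Quality control section already provides an amendment route.
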